#### 2.2.3. Withdrawal, Dropout, and Discontinuation

Participation will be discontinued if the participant has sudden worsening of condition that is not confirmed to be associated with this trial, or serious adverse events, or is unable to cooperate with the trial investigators and/or to complete the follow-up. If the condition continues to worsen, complications or special physiological changes emerge, a participant refuses to continue the trial, or a participant uses medicines that are not permitted in this trial, the patient will be withdrawn from the trial after the researcher's assessment. The data will be considered invalid but will still be included in the full analysis set (FAS). Information from dropouts will be collected by phone interviews, such as the reason for the trial discontinuation and the status of the final medication received. Participants who withdraw from the trial will receive appropriate treatment for adverse events.

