### 2.4. Outcomes and Measures

The primary indicators, HbA1c, fasting blood glucose (FBG), 2-hour postprandial blood glucose (2hPBG), and triglyceride (TG) levels, will be tested at T0, T1, T2, T3, and T4. The secondary indicators, ultrasonic cardiography (UCG) finding, coagulation indicator, and P- selectin level, will be assessed at T1 and T4. Cardiac death, nonfatal myocardial infarction, coronary revascularization, Seattle Angina Questionnaire (SAQ) score, and TCM symptom indicators will also be monitored periodically. Adverse events, which include hemorrhage, will be followed up using electrocardiography, routine urinalysis, routine stool test, and liver and kidney function tests (ALT, AST, Cr, and BUN) from T1 to T4. Items to be measured and the time window of data collection are shown in Table 1.

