### 2.9. Sample Size Calculation

The sample size was determined with a type I error rate of *α* = 0.05 and a power of 80% (type II error rate of *β* = 0.2). According to a previous study, the efficacy rate of Zhenyuan capsules is 94% for relieving angina pectoris symptoms and 64% for placebo [10]. The sample size should therefore consist of 25 participants in each group. Considering the potential 20% loss and the cases that can be counted in each center, 100 participants are needed for each group. As treatment and control groups, and three centers are involved, 200 participants will be recruited in this study. The formula used to calculate the sample size is as follows:(1)$$\begin{array}{c} n=\frac{p_{1}\left(1-p_{1}\right)+p_{2}\left(1-p_{2}\right)}{{\left(p_{1}-p_{2}\right)}^{2}}{\left(\;u_{1-\alpha }+u_{1-\beta }\;\right)}^{2}, \end{array}$$*n* ≈ 25 patients/group.

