### 2.10. Statistical Analyses

Statistical analyses will be conducted by an independent statistician from Xiyuan Hospital. In the FAS, patients will be dosed with the study drugs at least one time and one clinical observation will be recorded. Participants with good compliance and without any protocol deviations will be included in the per-protocol set (PPS). Subjects with safety data who have completed at least one study visit will be included in the safety analysis. The mean ± SD will be used in continuous variables. The characteristic comparability between the two groups will be evaluated by a two-sample Student *t*-test for continuous variables and the Fisher exact test or *χ*^2^ test for categorical variables. In this multicenter trial, the Cochran-Mantel-Haenszel test and the analysis of variance will be used. For diminishing the influence of confounding factors on the curative effect, analysis of covariance and the logistic regression model will be applied. For all the analyses, the difference with a value of *P* < 0.05 will be statistically significant. All analyses will be conducted using the SAS software version 9.3 (SAS Institute, Cary, NC, USA).

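### No week-12 blood test is planned for patients who leave the trial, although withdrawn patients stay in the FAS and all four primary indicators are blood tests

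*Protocol article*

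**What the plan says.** Section 2.4 names HbA1c, FBG, 2hPBG and TG as the primary indicators. They are measured at every visit: "triglyceride (TG) levels, will be tested at T0, T1, T2, T3, and T4". Table 1 shows the same schedule.

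Section 2.2.3 describes how patients leave. Participation is discontinued for sudden worsening, serious adverse events, or inability to cooperate or complete follow-up. After the researcher's assessment, a patient is withdrawn for continued worsening, complications, refusal or use of a medicine the trial does not permit. The sentence on data that follows keeps these patients in the FAS. For what is collected afterwards, the section says: "Information from dropouts will be collected by phone interviews, such as the reason for the trial discontinuation". It adds the status of the last medication and names no laboratory visit.

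Section 2.3 lets patients with type 2 diabetes continue their current glucose-lowering drugs but bars other treatments for angina and diabetes. Section 2.6 lists the four primary indicators among the baseline measures and has those measures repeated at T1 and T4 in all participants.

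Section 2.10 defines the FAS by at least one dose and one clinical observation. It names analysis of variance and the Cochran-Mantel-Haenszel test, and for confounders says that "analysis of covariance and the logistic regression model will be applied". Section 2.9 allows for loss: "Considering the potential 20% loss and the cases that can be counted in each center".

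**The concern.** The primary evidence consists of laboratory values, and the stated follow-up after exit cannot produce laboratory values. This is a data-collection rule that the protocol itself sets. A later analysis plan can choose a method for missing data, but it cannot recover blood that was never drawn.

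The loss is also unlikely to be neutral. Sections 2.2.3 and 2.3 together mean that a patient whose glucose control deteriorates, and who is then given a further diabetes treatment, may be withdrawn. Poor control can thus cause the absence of the measurement that would have shown it. If control differs between the arms, so may the loss. The FAS comparison of the primary indicators would then rest on a selected group, or on assumptions about values that a scheduled visit could have supplied.

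**Working it through.** **1. The passages side by side.**

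| Question | Section | What follows |
|---|---|---|
| Who leaves? | 2.2.3 | Patients who worsen, have serious adverse events, refuse, or use non-permitted medicines |
| Are they in the FAS? | 2.2.3, 2.10 | Withdrawn patients: stated. Others who leave: yes, if they had one dose and one observation |
| What is collected afterwards? | 2.2.3 | A phone interview of dropouts; no blood draw named |
| What does the FAS need? | 2.4 | Four blood tests, up to T4 |
| Who is measured at T4? | 2.6 | All participants |

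If all participants in 2.6 includes those who have left, 2.2.3 should say so. If it does not, the FAS contains patients with no planned T4 primary value. The two sections need reconciling either way.

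**2. The plan's own figures.** Section 2.9 assumes "94% for relieving angina pectoris symptoms and 64% for placebo" and concludes "The sample size should therefore consist of 25 participants in each group". With its formula:

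- p1(1 − p1) + p2(1 − p2) = 0.94 × 0.06 + 0.64 × 0.36 = 0.0564 + 0.2304 = 0.2868
- 0.2868 / 0.30² = 3.187
- 3.187 × (1.960 + 0.842)² = 25.01

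The 25 is reproduced with a two-sided 5% level. Allowing for 20% loss gives 25 / 0.8 = 31.25, or 32 per group, so the 100 per group does not come from the loss allowance alone. The calculation concerns angina relief, not a primary indicator. It supplies no SD or effect size for the four blood tests and no loss by arm.

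**3. Precision, if the 20% were realised as missing T4 values (assumption).** That leaves 80 of 100 per group. The effect detectable with 80% power is (1.960 + 0.842) × √(2/n):

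- n = 100: 0.396 SD
- n = 80: 0.443 SD

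For an assumed 0.40 SD effect, power is 80.7% with 100 per group and 71.6% with 80.

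**4. Bias in a completers' comparison (assumed inputs).** Let a and b be the loss fractions in the two arms and g the amount, in SD, by which lost patients are worse than completers in both arms. With no true effect, the bias is (b − a) × g.

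| Loss, a vs b | g = 0.5: bias, type I error | g = 1.0: bias, type I error |
|---|---|---|
| 20% vs 20% | 0, 5% | 0, 5% |
| 15% vs 25% | 0.05 SD, 6.1% | 0.10 SD, 9.7% |
| 10% vs 30% | 0.10 SD, 9.6% | 0.20 SD, 24.1% |

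With equal 20% loss, bias arises if the treatment effect differs between lost patients and completers. It is 0.20 × that difference: 0.05, 0.10 or 0.20 SD for differences of 0.25, 0.5 or 1.0 SD.

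**5. Use of T2 and T3 (simulation).** 1,500 trials per setting, 100 per arm, true T4 difference 0.40 SD, about 20% loss after T2 or T3, adjacent-visit correlation 0.5 or 0.7. Ranges cover the settings and repeat runs.

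| Method | Loss linked to worse current value, control arm | Loss unrelated to outcome |
|---|---|---|
| ANCOVA on completers | 0.32 to 0.35 | 0.40 to 0.41 |
| Last value carried forward | 0.41 to 0.49 | 0.36 to 0.37 |
| Likelihood-type analysis using T2 and T3 | 0.40 to 0.41 | not quoted |

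The completers' estimate is too small by (0.40 − 0.35)/0.40 = 12.5% to (0.40 − 0.32)/0.40 = 20%. Standard errors were about 0.13 to 0.16, and nearly the same for the completers' and likelihood-type analyses.

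**The case against.** Several stronger conclusions are tempting, and the article does not support them.

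- *That ANOVA or ANCOVA will drop these patients.* Section 2.10 gives no missing-data rule. One may stand in a full protocol or analysis plan not shown here, and its absence from a journal article is no fault. A completers' analysis is one possibility and not a stated plan.
- *That lost patients cannot be scored.* Those who leave after T2 or T3 have on-treatment values that imputation or a repeated-measures model can use. What is missing is a measured T4 value.
- *That follow-up is by phone only.* Section 2.2.3 does not say only and does not exclude a visit. It names no other contact.
- *That week 12 is the declared primary time point.* It is the last visit. No section names it as the primary analysis time.
- *That 40 of 200 FAS patients will lack a T4 value.* The 20% in 2.9 is an allowance for loss, and nothing equates that group with the withdrawn patients kept in the FAS.

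The numerical case is also limited. Every bias figure rests on assumed effects and loss patterns. The simulated informative loss acts in one arm and through observed values, which is the situation in which a likelihood-type method is unbiased by construction. Loss before T2, or driven by unobserved values, was not examined. Some patients who refuse or cannot continue would not attend a blood draw anyway.

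These objections narrow the point. They do not touch its core: 2.2.3 plans no laboratory measurement after exit for patients it keeps in the FAS, and 2.6 reads differently.

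**Conclusion.** The concern holds in a limited form. For patients who leave, the protocol names phone contact and plans no T4 HbA1c, FBG, 2hPBG or TG, while section 2.6 implies that everyone is measured at T4. Since worsening or a barred diabetes treatment can lead to exit, the missing primary values may depend on outcome and differ between arms.

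The direction and size of any bias are unknown. The figures above show only that plausible assumptions give anything from no bias to 0.20 SD, and that a 20% loss of T4 values would cut power by about 9 percentage points (80.7% to 71.6%) at an assumed 0.40 SD effect. This is an inexpensive improvement worth making, not a demonstration that the trial's result will be wrong.

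**What to change.** **Section 2.2.3.** State that patients who stop study drug or are withdrawn, and who still consent, are asked to attend the remaining scheduled visits, at least the T4 blood draw. State that these values enter the FAS. Keep the phone interview for the reason for leaving and the medication status. Make the wording agree with section 2.6, so that it is clear whether all participants includes patients who have left. The rules on which medicines are permitted and when treatment stops need not change for this.

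**Section 2.10 (preferable).** Analyse each primary indicator in the FAS with a repeated-measures model on T2, T3 and T4, adjusted for the T1 value and center, with treatment, visit and their interaction. Patients lost after T2 or T3 then contribute what was measured. Patients with no value after T1 still contribute nothing, so the model complements the T4 draw and does not replace it.

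**Cost.** A few sentences of protocol text, some extra attendance at visits already in the schedule, and slightly more analysis work in SAS, which the trial already uses. The model assumes that missingness depends only on observed values, so one sensitivity analysis of that assumption is needed. The collection rule has to be in place before patients leave, because the blood values cannot be obtained later.

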### 2.3. Intervention

Patients who meet all the inclusion and none of the exclusion criteria will be randomized into two groups as follows: (1) treatment group, 0.5 g of Zhenyuan capsule, 3 times/day, and (2) control group, 0.5 g of placebo, 3 times/day. According to the Guideline for the Diagnosis and Treatment of Chronic Stable Angina, participants can maintain the conventional drug treatments such as antiplatelet agents, statins, nitrates, anticoagulation drugs, *β*-blockers, calcium channel antagonists, angiotensin-converting enzyme inhibitors, or angiotensin II receptor antagonists. However, statins are the only Western medicine for lipid treatment. Patients diagnosed as having type 2 diabetes maintain the current Western medicines for hypoglycemic effects. To avoid discussing their medications among themselves, participants are advised to take the drugs at home and required to remain isolated from each other. In addition, the treatment allocation remains blind throughout the study. Participants will not be permitted to use other treatments for angina pectoris in CHD and diabetes, including TCM herbs and Chinese patent medicine. In the run-in period, any TCM medications for improving blood lipid or glucose levels will not be permitted.

### 2.4. Outcomes and Measures

The primary indicators, HbA1c, fasting blood glucose (FBG), 2-hour postprandial blood glucose (2hPBG), and triglyceride (TG) levels, will be tested at T0, T1, T2, T3, and T4. The secondary indicators, ultrasonic cardiography (UCG) finding, coagulation indicator, and P- selectin level, will be assessed at T1 and T4. Cardiac death, nonfatal myocardial infarction, coronary revascularization, Seattle Angina Questionnaire (SAQ) score, and TCM symptom indicators will also be monitored periodically. Adverse events, which include hemorrhage, will be followed up using electrocardiography, routine urinalysis, routine stool test, and liver and kidney function tests (ALT, AST, Cr, and BUN) from T1 to T4. Items to be measured and the time window of data collection are shown in Table 1.

### 2.5. Adverse Events

Participants are required to honestly report any changes in their symptoms. Any adverse events or unexpected toxic side effects that develop during the trial will be analyzed to determine the cause. These will be recorded and treated appropriately by the intervention administrators. In cases of severe adverse events, the participating patients are asked to take immediate measures to protect their safety and report the events to the Drug Supervision Bureau, the trial applicant, and the ethics committee within 24 hours.

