#### 2.2.1. Inclusion Criteria

Subjects are eligible for study participation if they meet the following criteria: (1) coronary angiography or coronary computed tomographic angiography shows that at least one of the main branches of the coronary artery has stenosis of at least 50%; (2) TG levels between 1.70 and 2.25 mmol/L and HbA1c level between 5.7% and 7%; (3) the TCM syndrome differentiation is Qi and Yin deficiency; (4) age between 45 and 75 years at screening; and (5) providing informed consent form.

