### 2.7. Randomization and Blinding

Eligible patients are randomly allocated to the treatment or control group in a 1 : 1 ratio. The randomization sequence will be recorded by staff at the sponsor unit. The researchers and outcome assessors participating in this study have no knowledge of the randomization sequence details. In addition, the results are kept in sealed, opaque, and stapled envelopes. They will be unsealed at the end of the outcome assessment. Emergency letters, including random codes and group assignments, are prepared by a statistician. If the blind code is exposed, patients will be excluded accordingly. Any of the following situations could call for a blind breaking and urgent measure: a serious adverse event, serious complication, or a deterioration in the patient's condition.

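### Section 2.5 makes the patients, not the site investigator, responsible for the 24-hour notice of severe adverse events

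*Protocol article*

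**What the plan says.** Section 2.5 (Adverse Events) gives three kinds of duty.

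- **Patients, in general:** "Participants are required to honestly report any changes in their symptoms".
- **Trial staff, for any adverse event or unexpected toxic effect:** the cause is analysed, and "These will be recorded and treated appropriately by the intervention administrators".
- **When an event is severe:** "the participating patients are asked to take immediate measures to protect their safety and report the events to the Drug Supervision Bureau". What follows in that sentence adds the trial applicant and the ethics committee as recipients and sets a 24-hour limit.

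Two other sections deal with serious adverse events. Section 2.2.3 makes them a reason to discontinue participation. Section 2.7 makes them a reason for unblinding: "Any of the following situations could call for a blind breaking and urgent measure: a serious adverse event". Neither says who notifies the authorities.

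**The concern.** In the severe-event sentence the patients are the subject of both verbs, so they are the ones who act and the ones who report. Patients cannot sensibly carry a duty to notify a drug regulator, a trial applicant and an ethics committee, and the rule fails outright when the patient has died or is incapacitated.

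Such events are foreseeable here. Section 2.2.1 requires stenosis of 50% or more in a main coronary branch, and section 2.4 lists "Cardiac death, nonfatal myocardial infarction, coronary revascularization" among the events to be monitored. At stake is prompt safety notification. Followed literally, the rule leaves nobody at the site with the task of informing the three bodies.

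**Working it through.** The article gives no figure to reproduce and no arithmetic settles the point. The check is a reading of every place where a reporting duty could be assigned.

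| Place | What it assigns | Gives the 24-hour notice to site staff? |
|---|---|---|
| 2.2.3 Withdrawal, Dropout, and Discontinuation | Discontinuation for serious adverse events; withdrawal on the researcher's assessment; treatment for those who withdraw | No |
| 2.4 Outcomes and Measures | Tests used to follow adverse events from T1 to T4 | No |
| 2.5, before the last sentence | Patients report symptom changes; intervention administrators record and treat events | No |
| 2.5, last sentence | Patients take protective measures and notify three bodies within 24 hours | No, the patients are named |
| 2.6 Study-Specific Visits and Procedures | Recording of adverse events from T1 to T4 | No |
| 2.7 Randomization and Blinding | Grounds for unblinding and urgent measures; emergency letters prepared by a statistician | No |
| Table 1 | Timing of safety assessments | No |

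Three things follow.

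1. The last sentence of 2.5 is the only expedited-notice rule in the article. It names the recipients, the deadline and the responsible party, and the responsible party is wrong. This is a misstatement, not a detail left to a fuller protocol.
2. The order of duties within 2.5 shows that the subject is misplaced. Patients already have a suitable duty, to report symptom changes, in a sentence of its own. Staff record and treat any adverse event. Read literally, the last sentence then moves the most demanding task, notifying a regulator about the gravest events, from staff to patients. That is unlikely to have been intended.
3. The two halves of the sentence are not equally exposed. Treatment of adverse events has a named staff role one sentence earlier, with support in 2.2.3 and 2.7. The notice has no such cover anywhere.

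The wording of the trigger also differs. Section 2.5 uses *severe*, while 2.2.3 and 2.7 use *serious*. The article defines neither term. *Severe* usually describes intensity and *serious* describes consequence, so replacing one with the other can change which events require the notice.

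**The case against.** The strongest reply is that this is a translation slip whose intended meaning is plain: the sentence asks for measures to protect the patients' safety, which is naturally a task for site staff. The article condenses a fuller protocol that may have the rule right, and nothing here shows that any site would follow the printed wording. That is fair. It limits the point to the article's text and makes the practical consequence conditional, but it does not make the sentence correct.

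Three stronger readings are tempting, and the article does not support them.

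- **Patients are left to manage their own emergencies.** The intervention administrators treat any adverse event, which includes severe ones, and section 2.7 provides for urgent measures when an event is serious. The protective-measures clause is badly worded, but care is covered.
- **Safety data or efficacy results are compromised.** Recording is assigned to the intervention administrators in 2.5 and scheduled in 2.6. No outcome, sample size or analysis depends on the misworded sentence.
- **A number of missed notices can be estimated.** The article gives no rate of serious events, nor of events that leave a patient unable to report. Section 2.2.2 also excludes refractory heart failure, NYHA grade IV, cardiogenic shock and an ejection fraction below 35%, which removes some of the highest-risk patients. Any count would rest on an assumed rate and on the further assumption that sites obey the slip.

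Two nearby details add little. That "Emergency letters, including random codes and group assignments, are prepared by a statistician" does not conflict with any rule on who sends a safety notice. The advice to take the drugs at home, in section 2.3, is there to keep patients from discussing their medication.

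**Conclusion.** The point holds for the article's wording. The only expedited-notice rule assigns the notice to the patients, together with the accompanying protective measures, and no other text gives the notice to site staff. The main defect is the misassigned notice.

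Its extent is one sentence covering three recipients and one 24-hour limit. No event count can be attached to it. It should be corrected, because it is an operative safety rule that cannot work when the patient is dead or incapacitated. It is not a flaw in the statistical design. The conclusion rests only on the printed text and makes no claim about the full protocol or actual practice at the three centers.

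**What to change.** Change the subject of the last sentence of 2.5. Suggested wording:

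> If a serious adverse event occurs, the investigator at the participating center will act at once to protect the participant and, within 24 hours, will notify the Drug Supervision Bureau, the ethics committee and the trial applicant.

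Patients keep only the duty to tell the site of symptom changes.

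This wording also replaces *severe* with *serious*, to match 2.2.3 and 2.7. The correction should state that change openly, because it may alter which events trigger the notice. If the sponsor does not intend it, keep *severe* and change only the subject.

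The cost is a one-sentence correction, with no extra staff, visits or procedures.
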